**List of Abbreviations**

ANOVA Analysis Of Variance

ACQ Asthma Control Questionnaire

CRP C - reactive protein

CV Cardiovascular

EBC Exhaled Breath Condensate

FEV_1_ Forced Expiratory Volume in the first second

FMD Flow-mediated dilation (% baseline)

FVC Forced Vital Capacity

HR Heart Rate

HREB Health Research Ethics Board

IL-6 Interleukin 6

IL-8 Interleukin 8

LT Lactate Threshold

PC_20_ Provocative Concentration yielding a 20% reduction in FEV_1_

PD_15_ Provocative dose yielding a 15% reduction in FEV_1_

PWV Pulse wave velocity (m/s)

RER Respiratory Exchange Ratio

SSRH Shear Stress during Reactive Hyperemia

TNFα Tumor Necrosis Factor alpha

VO_2max_ Maximal rate of oxygen consumption

VO_2peak_ Peak rate of oxygen consumption

VRH Velocity during Reactive Hyperemia

VTI Velocity Time Integral

# Introduction/Significance

This document is a clinical research protocol and the described study will be conducted in compliance with the protocol, Good Clinical Practices standards and associated Federal regulations (i.e Health Canada), and all applicable institutional research requirements.

Asthma is a chronic inflammatory disease characterized by pulmonary inflammation and bronchoconstriction, and the prevalence of asthma is steadily rising worldwide[^1^](#_ENREF_1). **Asthma and Cardiovascular Disease:**  While asthma is generally considered to be a disease of the airways, there are important systemic consequences which have predisposed people with asthma to become more likely to die from cardiovascular (CV) disease compared to non-asthmatics[^2^](#_ENREF_2). Additional CV risks have been reported in people with severe asthma[^3^](#_ENREF_3), and there is a relationship between reductions in lung function and cardiac death[^4^](#_ENREF_4). To date, little is known in regards to the interaction between asthma exacerbations and CV risk. **Asthma and vascular dysfunction:** Brachial flow-mediated dilation (FMD) is used as a non-invasive tool to evaluate endothelial function[^5^](#_ENREF_5). Brachial FMD is impaired in people with coronary dysfunction[^6^](#_ENREF_6), and can predict future CV events better than traditional CV risk factors[^7^](#_ENREF_7). People with asthma have previously been shown to have impaired endothelial function compared to non-asthmatics[^8^](#_ENREF_8), but the underlying mechanism(s) are unclear. **Asthma, Systemic Inflammation, and CV risk:** Chronic systemic inflammation is an established risk factor and predictor of future CV events[^9^](#_ENREF_9), and levels of systemic inflammation are increased in asthma[^10^](#_ENREF_10)^,^[^11^](#_ENREF_11). Furthermore, while people with high levels of inflammation are more likely to suffer both first time and recurrent cardiac events[^12^](#_ENREF_12)^,^[^13^](#_ENREF_13), levels of systemic inflammation in asthma are related to disease severity and are the highest during asthma exacerbations[^10^](#_ENREF_10)^,^[^11^](#_ENREF_11). Previous studies have shown that systemic inflammation directly impairs vascular function[^14^](#_ENREF_14), and rodent work has shown that pulmonary inflammation can impair vascular function[^15^](#_ENREF_15). To-date no study has examined how an asthma attack may affect vascular function and CV risk. Thus, to gain better understanding of the increased CV risks associated with asthma exacerbations, *the first aim of this study is to evaluate how acutely increasing pulmonary inflammation affects vascular function* in people with asthma. **Physical activity and the immune system:** Physical inactivity has previously been associated with increased systemic inflammation[^16^](#_ENREF_16), while higher levels of physical activity can reduce inflammation[^17^](#_ENREF_17) and vascular dysfunction[^18^](#_ENREF_18)^,^[^19^](#_ENREF_19). Acute exercise has been shown to modulate the systemic responses to inflammatory insults[^20^](#_ENREF_20), and being more physically active is associated with better asthma symptoms[^21^](#_ENREF_21) but whether acute exercise influences the systemic responses to asthma exacerbations is unknown. The second aim of this study is to *assess the influence of acute exercise on the systemic and vascular responses to acute pulmonary inflammation* in asthma.

# Study Objectives

***Primary Objective***

To examine the acute impact of pulmonary inflammation and bronchoconstriction on systemic inflammation and vascular function in asthma.

***Secondary Objective***

To evaluate the influence of *acute* exercise on systemic inflammatory and vascular responses to acute pulmonary inflammation.

# Patients and Methods

## Study Design

### General Design

This study is a case-control study utilizing a repeated measure design. Each participant will undergo a series of bronchial challenges trials, including

- Mannitol challenge
- Methacholine challenge
- Placebo (control) challenge.

Vascular parameters such as flow mediated dilation (FMD; endothelial function) and pulse wave velocity (PWV; arterial stiffness) will be evaluated before, immediately after, 1 hour after, and 24 hours after each challenge. Blood samples will be obtained for analysis of systemic inflammatory response and exhaled breath condensate will be collected for analysis of pulmonary inflammation and oxidative stress at each time-point.

For the secondary objective, the subjects will in a random order either exercise for 30 minutes or rest for 30 minutes before being subjected to either a placebo challenge or a mannitol challenge, in a cross-over design. The same parameters as for the primary objective will be evaluated before, immediately after, 1 hour after, and 24 hours after each challenge.

1. ***Case-control studies***

*Definition of study groups:*

Asthmatics, defined according to CTS criteria[^22^](#_ENREF_22), will be recruited for the study. This repeated measure design will minimize the risk of between-groups variability and match the case and the control group on all variables except the experimental parameters within the different trails.

*Blinding and avoiding bias:*

All subjects will be blinded to what bronchial challenge is administered. The challenges will be administered in random order and the research staff performing the vascular function analysis will be blinded to what challenge the participant has undergone within each trail.

### Primary Outcome Variable

Flow-mediated dilation (FMD) of the brachial artery following 5 minutes of forearm occlusion will be measured using our ultrasound machine (8L-RS 4.0-13.0 MHz probe, Vivid q, GE Healthcare, Mississauga, ON) and FMD data will be analyzed using FDA approved software available from Medical Imaging Applications (Coralville, IA, USA). FMD will be calculated as: (peak hyperemic diameter-baseline diameter)/baseline diameter x 100. Peak hyperemic brachial arterial velocity (and subsequently shear stress) will be determined using Doppler ultrasound, and used for normalization of FMD.

### Secondary Outcome Variables

Arterial stiffness will be determined using carotid – femoral pulse wave velocity (PWV), and PWV will be calculated from measurements of pulse transit time and the distance traveled by the pulse between recording sites.

## Subject Selection and Withdrawal

### Inclusion Criteria

To be eligible for this study, the participants have to be between the ages of 18 and 65, have a body mass index of less than 35 kg/m^2^, controlled or partly controlled asthma according to the Asthma Control Questionnaire[^23^](#_ENREF_23)^,^[^24^](#_ENREF_24).

### Exclusion Criteria

Subjects who at the time of the study have one or more risk factors for CV disease[^25^](#_ENREF_25), known CV disease, other lung diseases then asthma, current infections, or are pregnant will be excluded from the study.

## Study Procedures

*Measurements*

*Pulmonary function* – all participants will undergo a full pulmonary function test, according to established clinical guidelines[^26^](#_ENREF_26)^,^[^27^](#_ENREF_27). The expiratory volume in 1 second (FEV_1_) responses to 4x100 mg Salbutamol will be evaluated, and an increase in FEV_1_ of ≥ 12% and 200 ml will be considered positive for reversible airway constriction[^22^](#_ENREF_22).

*Endothelial function -* The endothelial function of the brachial artery will be evaluated after 10 minutes of rest in the supine position using ultrasound imaging (8L-RS 4.0-13.0MHz probe, Vivid q, GE Healthcare, Mississauga, ON). Baseline diameter of the brachial artery will be established, whereby the blood flow of the forearm will be occluded distally of the measuring site for the duration of 5 minutes. Upon release of the occlusion, the blood velocity and the brachial diameter will be monitored for 3 minutes, and later analyzed (Medical Imaging Applications, LLC, Coralville, IA, USA; EchoPAC PC software, version 110.x.x, GE Healthcare, Horten, Norway). Microvascular function will be evaluated as the velocity time integral-envelope of the first heartbeat of reactive hyperemia (VTI; m/s) and the velocity during reactive hyperemia (VRH) calculated as VTI x 60/HR[^28^](#_ENREF_28). Shear stress during reactive hyperemia (SSRH) will subsequently then evaluated as 8 x 0.035 x blood velocity/(baseline diameter/10) at peak velocity and as cumulative SSRH until the time of peak FMD%[^29^](#_ENREF_29)^,^[^30^](#_ENREF_30). FMD/SSHR will be considered the main outcome for endothelial function in this study, and VRH and SSRH as indicators of microvascular function. All tests will be conducted after a 12 hour fasting period. Where applicable, the subjects will be asked to withhold any long-acting asthma medication for a minimum on 48 hours prior to the test, and short-acting asthma medications for 12 hours prior to the test.

*Arterial stiffness* - Arterial stiffness will be evaluated using pulse wave velocity (PWV) between the carotid and femoral arteries. After 10 minutes of supine rest, the time of the up-stroke of 30 pulse waves will be collected simultaneously using applanation tonometry (Mikro-tip Catheter Transducers model SPT-301, MillarInstruments, Inc., Houston, TX, USA) over the femoral and the carotid arteries. The sites of measurement will be temporarily marked, whereby the distances between the markings and the sternal notch will be measured. The tonometry signal will be recorded using the Powerlab acquisition system (Powerlab, 16/30, ADInstruments, New South Wales, Australia). A total of 10 consecutive beats will be selected for analysis (LabChart version 7.3.5 ADInstruments, New South Wales, Australia) and the timing of each upstroke will be manually adjusted to minimize potential errors throughout the steps of analysis. After receiving a time-stamp for each beat, delta-time (Δt) will be calculated as the difference between the time of the up-stroke of the waveform at the femoral artery and the carotid artery (Δt = femoral waveform – carotid waveform). The distance (d) will be calculated as the difference between the distance from the sternal notch to the femoral artery and the sternal notch to the carotid artery. PWV was then calculated as d/Δt and expressed in meters per second (m/s)[^31^](#_ENREF_31). Beat-to-beat blood pressure will be measured throughout the test (Finapres Medical Systems, Amsterdam, The Netherlands) and the signal will be calibrated offline to brachial blood pressure also recorded at the time of testing. The heart rate will be monitored using 1-lead echocardiography (Dual Bio Amp, ADInstruments, New South Wales, Australia).

*Systemic inflammation -* To minimize number of venous punctuations, an intra-venous catheter will be inserted in an antecubital vein on the first day of each experimental day. Upon insertion, the catheter will be flushed with 0.9% NaCl. Blood will be collected before, immediately after, and 1 hour after after each challenge. Before each blood draw, approximately 3 ml of blood will be discarded whereby the sample will be collected. The catheter will then be flushed again with 0.9% NaCl. The catheter will be removed before the subject leaves the laboratory. A single blood draw will be performed at the 24 hour follow-up assessments. All blood samples will be collected in anti-coagulant-free tubes pre-labeled with the assigned subject identification number, date, and time-point. Once collected, the blood will be left allowed to clot in room temperature for a minimum of 30 minutes before being centrifuged at 1000g for 10 minutes at 4 degree Celsius. Serum will then be separated into aliquots of 100 µl immediately following centrifugation. The aliquots will be stored at -80 degrees Celsius and later outsourced to Eve Technologies, Calgary, AB, for analysis of inflammatory markers (i.e. of IL-6, IL-8, TNFα, and CRP).

*Pulmonary inflammation -* Exhaled breath condensate (EBC) will be collected in quantities of 1-2 mL before, immediately after, 1 hour after, and 24 hours after each bronchial challenge using commercially available collection tubes (RTube™ Respiratory Research, Inc., Austin, TX, USA). The subjects will be asked to breathe normally into a mouthpiece with their nose occluded for 10 minutes. The mouthpiece will be connected to a collection chamber that is covered in a cooling sleeve which allows for the exhaled breath to condense. A one-way valve keeps the EBC in the upper part of the collection tube, from where it will be extracted into aliquots for storage in -80°C until further processing. All EBC sample will be outsourced to Eve Technologies, Calgary, AB, for analysis for CRP and 8-isoprostane.

*Bronchial challenges*

*Mannitol challenge -* The mannitol challenge will be conducted according to the protocol created and validated to the methacholine challenge by the inventor[^32^](#_ENREF_32); dry powder mannitol (Aridol®, Pharmaxis Inc., Exton, PA, USA) will be inhaled in concentrations of 0, 5, 10, 20, 40, 80, 160, 160 and 160 mg mannitol, for a total cumulative dose of 653 mg. Spirometry, as described previously, will be performed before the first inhalation to receive baseline lung function values, and at 1 minute following each of the doses. The value for FEV_1_ following the inhalation of 0 mg mannitol will be the reference value used for comparison for the remainder of the challenge. The challenge will be considered positive if a cumulative concentration of ≤ 635 mg mannitol yield a reduction in FEV_1_ of ≥ 15% compared to baseline (0 mg mannitol) FEV_1_ (PD_15_; provocative dose yielding a 15% reduction in FEV_1_) whereby the challenge will end. A cumulative dose of 635 mg will be used as the maximum dose for when/if a mannitol challenge does not resulted in a ≥15% reduction in FEV_1_ (negative tests).

As shown previously[^32^](#_ENREF_32), the FEV_1_ will in most people spontaneous recovery to within 95% of baseline values within 60 minutes following the last mannitol inhalation and reliever medication will not be required. Capillary oxygen saturation will be monitored throughout the challenge (Radical 7, Masimo, Neuchatel, Switzerland), including the recovery, and the FEV_1_ will be measured every 10 minutes following the last inhalation of mannitol until the FEV_1_ has returned to within 95% of baseline values. In case of an unexpected severe bronchoconstriction following the last inhalation of mannitol, the subject will be given 400 mg Salbutamol (Ventolin® inhaler)[^32^](#_ENREF_32) to relax the airways. A physician will be available for supervision of all mannitol challenges.

*Methacholine challenge –* The participants will perform a baseline spirometry test whereby they will be asked to inhale cumulative concentrations of methacholine until there is ≥20% reduction in FEV_1_ or test last concentration (16 mg/ml) has been used. During the challenge, methacholine powder, diluted in sterile saline at concentrations of 0.031, 0.0625, 0.125, 0.25, 0.5, 1, 2, 4, 8, and 16 mg/ml, will be administered with a nebulizer according to a 2-minute tidal breathing protocol where the subject performs a FEV_1_ test 30 and 90 seconds after each 2 minutes of methacholine at incremental concentrations[^33^](#_ENREF_33). The tests will end if PC_20_ is reached or if the highest concentration of methacholine (16 mg/ml) is given[^22^](#_ENREF_22). If the test results in a reduction in FEV_1_ below 95% of baseline values, the FEV_1_ will be monitored every 10 minutes until spontaneous recovery to within 5% of baseline FEV_1_, or reversed using 4 puffs (100 mg/puff) Salbutamol. Capillary oxygen saturation will be monitored throughout the challenge (Radical 7, Masimo, Neuchatel, Switzerland).

*Placebo challenge -* The protocol for the placebo challenge will be identical to the protocol for the methacholine challenge, with the exception that no methacholine will be added to the inhaled saline mixture. The subject will be blinded to the fact that no methacholine has been added and will be monitored as if a potential severe bronchoconstriction could occur, identical to the methacholine challenge.

*Exercise trial*

*Cardiopulmonary exercise test* - A graded cardiopulmonary exercise test will be performed to determine the rate of oxygen consumption (VO_2max_) at maximal exercise and the power output at which the subjects reach their anaerobic threshold (AT). The test will be performed on a cycle ergometer (Ergoselect 200, Ergoline, Bitz, Germany) at incremental stages (25 watts increase/2 minute until the AT is reached, and then in steps of 25 watts/1 minute until exhaustion). While performing the fitness test, the subject will be breathing though a mouthpiece connected to a Vmax Metabolic Cart (CareFusion, Yorba Linda, CA, USA), allowing for breath to breath analysis of pulmonary gases. Throughout the test, the heart rate (HR) responses will be monitored, and ECG recorded. The subjects will also be asked to rate the level of perceived exertion at two-minute intervals during the test, expressed on a Borg scale from 1 (no exertion) to 10 (exhaustion). Blood pressure measurements will be taken at rest and every two minutes. VO_2max_ will be confirmed if the following criteria are met: 1) plateau in VO_2_, 2) respiratory exchange ratio (RER) ≥ 1.1, 3) HR ≥ 90 % of predicted maximum, 4) patient exhaustion/Borg scale > 9/10, or 5) evidence of respiratory limitations. In the absence of a plateau in VO_2_ where remaining criteria for a maximal test were met, the highest recorded VO2 value will be referred to as VO_2peak_ and used as a substitute for VO_2max_ as a measurement of cardio-pulmonary fitness[^34^](#_ENREF_34).

The power output at AT will be noted, and a power output of 25 watts below the AT power output will be chosen for the 30 minute exercise protocol for the second objective of the study. In addition, the pulmonary responses to exercise will be established by spirometry before and after exercise.

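### The formula for hyperaemic velocity (VRH = VTI x 60/HR) multiplies by beat duration instead of dividing by it, so VRH is not a velocity and its error depends on heart rate

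*Protocol*

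**What the plan says.** The List of Abbreviations has "VTI Velocity Time Integral" and "VRH Velocity during Reactive Hyperemia", so VTI is an integral and VRH is a velocity. In section 3.3, Study Procedures, the paragraph on endothelial function takes VTI as the "velocity time integral-envelope of the first heartbeat of reactive hyperemia (VTI; m/s"), and then gives "the velocity during reactive hyperemia (VRH) calculated as VTI x 60/HR".

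The same paragraph computes shear stress during reactive hyperaemia (SSRH) as "8 x 0.035 x blood velocity/(baseline diameter/10) at peak velocity and as cumulative SSRH until the time of peak FMD"%. It assigns the roles as follows: "FMD/SSHR will be considered the main outcome for endothelial function in this study, and VRH and SSRH as indicators of microvascular function" (SSHR is read here as SSRH).

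Section 3.1.2, Primary Outcome Variable, defines FMD from arterial diameters alone and adds: "Peak hyperemic brachial arterial velocity (and subsequently shear stress) will be determined using Doppler ultrasound, and used for normalization of FMD".

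**The concern.** The heart-rate factor appears to be upside down. Converting a distance travelled in one beat into a velocity means dividing by the length of the beat, and the printed formula multiplies by it. The protocol handles the parallel step correctly for pulse wave velocity, where distance is divided by transit time and the result is given in m/s.

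A constant error would drop out of comparisons within a subject, but this one varies with heart rate. Section 3.1.1 measures the vascular parameters before each challenge, immediately after it, and at 1 and 24 hours. For the second objective it compares 30 minutes of exercise with 30 minutes of rest. If heart rate differs between these conditions, the difference enters VRH with the wrong sign and could be read as a microvascular effect.

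**Working it through.** **Inputs from the protocol.** VTI is an integral over one beat, with printed unit m/s. VRH is named a velocity and computed as VTI x 60/HR. **Assumed for illustration:** all heart rates and VTI values, because the documents give none.

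**Dimensions.** Beat duration is RR = 60/HR seconds.

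- VTI as a distance, as its name implies: VTI x 60/HR has unit m x s = m·s.
- VTI in m/s, as printed: VTI x 60/HR has unit m/s x s = m.
- Mean velocity over the beat is VTI/RR = VTI x HR/60, with unit m/s when VTI is in m.

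The printed formula therefore gives a velocity under neither reading of the unit.

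**Size when VTI is a distance.** Printed/true = (VTI x 60/HR) / (VTI x HR/60) = (60/HR)^2. As a check, a synthetic one-beat waveform with a known mean velocity of 0.60 m/s was integrated numerically at several heart rates:

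| HR (bpm) | VTI (m) | VTI x 60/HR | VTI x HR/60 | Printed/true |
|---|---|---|---|---|
| 50 | 0.720 | 0.864 | 0.600 | 1.44 |
| 60 | 0.600 | 0.600 | 0.600 | 1.00 |
| 75 | 0.480 | 0.384 | 0.600 | 0.64 |
| 90 | 0.400 | 0.267 | 0.600 | 0.44 |
| 100 | 0.360 | 0.216 | 0.600 | 0.36 |

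The HR/60 form recovers 0.60 m/s at every rate. The printed form does so only at 60 bpm, where the two coincide.

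**Direction.** Let heart rate change by a factor h and VTI by a factor v. True velocity changes by v x h, and printed VRH by v/h. When heart rate rises (h > 1), the two move in opposite directions whenever 1/h < v < h, that is, whenever VTI changes proportionally less than heart rate.

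- HR 60 to 75, VTI fixed at 0.60 m: true velocity goes from 0.60 to 0.75 m/s (+25%), printed VRH from 0.60 to 0.48 (-20%). With h = 1.25, reversal occurs for any v between 0.80 and 1.25.
- HR 65 to 80, VTI up 10%: true 1.1 x 80/65 = 1.354 (+35.4%), printed 1.1 x 65/80 = 0.894 (-10.6%).
- If VTI rises proportionally more than heart rate (v > h), both rise and there is no reversal, though the printed size is still wrong.

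**Size if the recorded quantity is already a beat-averaged velocity in m/s.** No heart-rate factor is then needed. The printed product is a distance, numerically 60/HR times the velocity: 0.80 at 75 bpm and 0.67 at 90 bpm. It is still not VRH.

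**Where the error goes.** FMD is a ratio of diameters and contains no velocity. SSRH uses "8 x 0.035 x blood velocity/(baseline diameter/10"), evaluated at peak velocity and cumulatively up to peak dilation. VRH is a single value from the first beat and cannot supply a cumulative series. Section 3.1.2 takes the velocity for normalisation from Doppler. No statement in the protocol puts VRH into SSRH.

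**The case against.** The strongest reply is that the formula carries a literature citation and may be a slip in transcription that staff would not follow. The source is not at hand, so this cannot be settled. The printed line is nevertheless the protocol's instruction, and it contradicts the protocol's own definitions whatever the source says.

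A second reply is that heart rate may differ little when the artery is scanned: FMD follows 10 minutes of supine rest, and exercise comes before the challenge. Salbutamol is conditional on the airway response, so it is not a planned difference between conditions. This stands as a limit on size. The percentages above illustrate the mechanism and do not forecast this trial's heart rates.

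A third reply is that the correct repair depends on what is recorded. If the printed unit is right and the name is wrong, VTI x HR/60 would also be wrong. This stands, and the fix allows for it.

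Two stronger readings are tempting. A reader might infer that the error passes into SSRH and so into FMD/SSRH, because VRH is the only velocity given a formula and SSRH is described next. The text does not support this: section 3.1.2 names Doppler peak velocity, and section 3.3 applies shear at peak velocity and cumulatively. A reader might also infer that SSRH comes out 100 times too small, because dividing diameter by 10 suggests cm while m/s is printed nearby. But that m/s is attached to VTI, no unit is given for the blood velocity in the shear formula, and a constant factor would cancel in comparisons and leave the ANOVA F tests unchanged.

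**Conclusion.** The formula is wrong as written. It multiplies by beat duration where it should divide, or applies a heart-rate factor where none is needed, and it yields a velocity under neither reading of VTI's unit. With VTI as a distance, VRH is wrong by (60/HR)^2, for example 0.64 at an assumed 75 bpm and 0.44 at 90 bpm. The error survives within-subject comparisons if heart rate differs, and it reverses the direction of change when heart rate rises and VTI changes proportionally less.

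The damage is confined to VRH, one of the named microvascular indicators. FMD is unaffected. SSRH and FMD/SSRH are unaffected provided they are computed from Doppler velocity as section 3.1.2 indicates. This is a correction that should be made before VRH is derived or analysed. It does not threaten the primary outcome, the sample size or the conduct of the study.

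**What to change.** In section 3.3, Endothelial function:

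1. Give VTI in m or cm and write VRH = VTI x HR/60, with 60/HR taken as the R-R interval of the beat measured. If the recorded quantity is already a beat-averaged velocity in m/s, rename it and drop the heart-rate factor.
2. State that the blood velocity in the SSRH formula is the Doppler velocity of section 3.1.2, in cm/s to match diameter divided by 10.
3. Recompute any VRH already derived.

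The cost is a line or two in the protocol and one in the derivation program. Section 4.2 keeps all data for 5 years after completion, so recomputation should be possible if VTI and the heart rate of the same beat were recorded.

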## Statistical Plan

### Sample Size Determination

We do not know the anticipated effect of our interventions on FMD; however, based on previous studies[^8^](#_ENREF_8), a total of 20 subjects per group will be sufficient to detect a difference in FMD between trials (α=0.05, power=0.8). An additional 10 subjects per group will be recruited to account for dropouts. Thus, 60 subjects will be recruited for aim 1 and 60 subjects will be recruited for aim 2.

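### Salbutamol may be given freely after methacholine but only for severe bronchoconstriction after mannitol, so the 1-hour methacholine FMD can mix bronchoconstriction with bronchodilator exposure

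*Protocol*

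**What the plan says.** All of this is in the Protocol.

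- **Outcome and schedule.** FMD of the brachial artery is the primary outcome (Primary Outcome Variable). General Design schedules it "before, immediately after, 1 hour after, and 24 hours after each challenge".
- **Withholding.** The endothelial-function paragraph of Study Procedures asks participants, where applicable, to stop long-acting asthma medication for at least 48 hours and "short-acting asthma medications for 12 hours prior to the test". The preceding sentence is the fasting rule: "All tests will be conducted after a 12 hour fasting period".
- **Methacholine.** The challenge stops at a fall in FEV1 of at least 20% or at the top concentration. If FEV1 is below 95% of baseline, it is checked every 10 minutes until it recovers unaided, "or reversed using 4 puffs (100 mg/puff) Salbutamol". No criterion decides between the two courses, and no time is given for the salbutamol.
- **Mannitol.** The challenge stops at a fall of at least 15% or at the maximum dose. Most people are expected to recover within 60 minutes, so that "reliever medication will not be required". Salbutamol has a narrow trigger: "In case of an unexpected severe bronchoconstriction following the last inhalation of mannitol, the subject will be given 400 mg Salbutamol".
- **Placebo.** The procedure is that of methacholine, "with the exception that no methacholine will be added to the inhaled saline mixture".
- **Analysis.** Statistical Methods plans a 2-way ANOVA for the interaction of the three trials with the four measurement times. Sample Size Determination states that "a total of 20 subjects per group will be sufficient to detect a difference in FMD between trials", at α = 0.05 and power 0.8.

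**The concern.** The three challenges are compared within person on FMD, but their reliever rules differ. After methacholine, salbutamol is open to staff for any fall of more than 5%. After mannitol it is for severe cases. After placebo the trigger should rarely be met. Exposure to a bronchodilator before the 1-hour FMD can therefore vary along the very contrast that the ANOVA tests.

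The usual protections do not reach this. Random order, blinding of the staff who analyse vascular function, and the within-person design all leave it in place, because the drug is given as a consequence of the challenge. If some methacholine sessions include salbutamol and the others mostly do not, a methacholine-placebo or methacholine-mannitol difference at 1 hour cannot be put down to bronchoconstriction alone. That attribution is the primary objective.

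**Working it through.** **1. The reliever rules side by side**

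| Challenge | When salbutamol may be given | Timing relative to FMD |
| --- | --- | --- |
| Methacholine | Any FEV1 below 95% of baseline, as an alternative to waiting | Not stated |
| Mannitol | Unexpected severe bronchoconstriction | Not stated |
| Placebo (saline) | As methacholine, but should seldom be triggered | Not stated |

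A session that reaches the methacholine end-point has FEV1 at or below 100% − 20% = 80% of baseline. It is therefore below the 95% limit, and every such session is open to salbutamol. A dose given between the end of the challenge and the 1-hour FMD precedes that FMD by at most about 1 hour. The text permits this but does not require it. The same silence leaves the measurement immediately after the challenge unprotected.

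**2. Which comparisons are exposed**

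There are 3 trials × 4 times = 12 cells, and the one mainly exposed is methacholine at 1 hour. The contrasts affected are methacholine-placebo and methacholine-mannitol at that time. Mannitol-placebo is barely touched. Aim 2 uses only mannitol and placebo. The 24-hour FMD normally falls more than 12 hours after any dose.

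**3. Illustrative size**

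The protocol gives no effect size or SD for its 20 subjects, so its power statement cannot be reproduced. As a yardstick, a paired t-test with n = 20, two-sided α = 0.05 and 80% power detects 0.66 SD of the within-person difference (noncentral t).

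Two inputs are assumptions that the documents do not supply: the share p of methacholine sessions reversed before the 1-hour FMD, and the shift δ in FMD due to salbutamol, in SDs of the within-person between-trial difference. No placebo or mannitol session is taken as reversed. The mean shift in the 1-hour methacholine-placebo difference is p × δ.

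Two tests were simulated with n = 20: a single paired t-test at 1 hour, and the planned trial-by-time interaction as a repeated-measures ANOVA (3 trials, 4 times, independent errors, SD of a between-trial difference equal to 1).

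| p | δ (SD) | p × δ (SD) | Share of 0.66 | Rejection with no true effect: paired test | Rejection with no true effect: planned interaction |
| --- | --- | --- | --- | --- | --- |
| any | 0 | 0 | 0% | 5% | 5% |
| 25% | 0.25 | 0.0625 | 9% | about 6% | about 5% |
| 50% | 0.5 | 0.25 | 38% | about 18% | about 10% |
| 75% | 0.5 | 0.375 | 57% | about 34% | about 18% |

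The interaction test reacts less because one shifted cell is spread over (3 − 1) × (4 − 1) = 6 degrees of freedom. If the shift instead opposed a true effect of 0.66 SD, the power of the paired test would fall from 80% to about 71%, 39% and 22% in the last three rows.

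**The case against.** **A contradiction with the withholding rule.** A reader might infer that salbutamol after methacholine breaks the protocol's own 12-hour rule, leaving the 1-hour FMD at least 11 hours short. The text does not support that firmly. The rule is something that participants are asked to do, it sits beside the fasting rule, and no other withholding rule appears in the challenge sections. It most naturally governs their own medicines before the visit, not rescue given by staff afterwards. Nor does the protocol give a reason for withholding, so it cannot be taken as evidence that short-acting drugs change FMD. This objection stands, and the point does not rest on that rule.

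**Permission, not instruction.** Spontaneous recovery is named first, and staff could leave salbutamol until after the 1-hour measurements. That also stands. The weakness is that nothing tells them to.

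**Size.** No section says that salbutamol alters FMD. A zero effect is possible, and the paired-test rates exceed those of the planned test. Both are accepted, and the table shows them.

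**Safety.** Methacholine is taken to a deeper fall than mannitol (20% against 15%). Physician supervision is promised for mannitol and not mentioned for methacholine, so a readier reliever there may be deliberate. That is a reason to leave rescue unrestricted. It does not justify having no criterion for the milder cases.

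**Left to other documents.** How FMD values after rescue are analysed may properly belong to an analysis plan that is not shown. The protocol's list of data to be collected does not name rescue salbutamol, but the appended forms are not at hand and may include it. The difference in the reliever rules is set in the protocol itself, and analysis cannot remove it.

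**Conclusion.** The concern holds as a fault in the methacholine procedure, limited in scope. As written, the protocol lets bronchodilator exposure before the 1-hour FMD differ by challenge, and where that happens the methacholine contrasts at 1 hour are confounded.

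The size is unknown. With no effect of salbutamol on FMD, or no early dosing, there is no bias. Under the assumed range (shift of 0.25 to 0.5 SD in 25% to 75% of methacholine sessions, 20 participants, no true effect), the planned interaction test rejects about 5% to 18% of the time, and a single paired test at 1 hour about 6% to 34%. These are illustrations, not estimates for this trial. The change is worth making because the exposure falls on the primary outcome and is cheap to avoid.

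**What to change.** In the methacholine paragraph, and for all three challenges alike, state that:

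1. FEV1 is measured every 10 minutes and spontaneous recovery is the default.
2. Salbutamol is given before the 1-hour measurements whenever staff judge it clinically necessary, and is never withheld for the study.
3. Otherwise, anyone still below 95% of baseline receives it after the 1-hour measurements.
4. The time and dose of any salbutamol are recorded, so that FMD values taken after it can be identified.

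A few words in the endothelial-function paragraph, saying that withholding applies before the challenge-day baseline, would also prevent the misreading described above.

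The cost is a few sentences and one recorded item. Some participants would wait up to about an hour after methacholine with reduced FEV1, which the protocol already permits. The 60-minute recovery expectation is stated for mannitol only, so methacholine recovery may take longer, and the physician cover promised for mannitol may need to be available for methacholine too.
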